### **5.1.2 Dosage and Route of Administration**

The intervention will be delivered face-to-face by the MCH nurse to the participating woman and any family members she chooses to be present. Nurses will deliver a minimum of 25 visits over the

course of the intervention. Nurses are recommended to limit the total number of visits to 35. It is suggested that families with a greater need should be referred to other community supports and health providers for additional support.

## **5.2 Measurement of subject compliance**

Subject compliance will be measured with fidelity instruments completed at every home visit, which are yet to be finalised but will be based on those used for MESCH (see **Appendix 8** and **Appendix 9** for antenatal and postnatal checklists, respectively). The checklists are used to record intervention delivery and fidelity only, and will not be seen by researchers assessing families. We will submit the fidelity measures for ethical approval once finalised for right@home. Significant non-compliance is defined as missing 6 months of the program, i.e. if no attendance for 6 months.

## **5.3 Excluded medications and treatments**

Families taking part in the Victorian Department of Human Service Cradle to Kinder (CtK) program or the Tasmanian CU@home program will not be eligible for the right@home study. CtK is an intensive support program for very vulnerable, teenage Australian mothers to prevent involvement in the Child Protection System. CU@home is a home visiting program designed for first-time mothers aged 15-19 years old. CtK and CU@home families are excluded from right@home because the programs are too intensive and complex for families to participate in both. The total number of CtK families is small (i.e. n~250) and recruited across Victoria, so we expect very few CtK families to be eligible families from the three Victorian right@home sites. Similarly, Tasmanian first-time mothers aged 15-19 years will only make up a small proportion of the right@home sample, and only around half of these mothers engage with the CU@home program.

# **6. SUBJECT ENROLLMENT AND RANDOMISATION**

## **6.1 Recruitment**

*Pre-recruitment preparation:* Following introductory emails sent by [name] (Victorian Department of Health) to Victorian antenatal clinic managers, and [name] (Tas Department of Health and Human Services) to Tasmanian antenatal clinic managers (see **Appendix 10** and **Appendix 11**), our research team has been in contact with managers at each antenatal hospital to discuss the right@home trial and identify which locations the right@home recruitment could feasibly take place. The local councils listed in Section 1.1 have signed or are in the process of signing contract agreements (see Appendices 25-29 for completed contracts). Since August 2012, our research team has had ongoing email and phone contact with the maternity staff at each site to determine the specifics of recruitment, e.g. to ascertain birth rates, to decide which clinics our research staff will recruit from, and to answer questions raised by the antenatal managers.

At the beginning of each recruitment session, i.e. before an antenatal clinic begins, researchers will briefly talk with clinic staff and provide a one-page information sheet that describes the study to staff (**Appendix 12**). Many of the clinic staff will already know about the study, but this ensures that all clinic staff know about right@home in a systematic and standardised way. An A3-sized poster describing the right@home study (**Appendix 13**) will be displayed in each antenatal clinic and, if women request information about the study before the researcher has an opportunity to speak with them, clinic staff can refer women to a flyer that our research team will print and make available in each waiting room (**Appendix 14**).

*Recruitment:* Potential participants will be all women who are pregnant, attending the antenatal clinics at the site hospitals listed in Section 1.1 and who fulfil the eligibility criteria outlined in Section 6.2. The recruitment and assessment process for the right@home trial are summarised in the Study Design Diagrams in Section 4.2. A short screening survey based on the pilot survey (see **Appendix 15**) will be used to identify eligible women for the right@home trial (see Eligibility criteria in Section 6.2). A trained research assistant will attend each antenatal clinic and approach all women in the waiting rooms. The researcher will describe the study (see script in **Appendix 16**) and ask whether women might be interested in taking part. At this first contact, researchers will ask women to reiterate what they are asking of the potential participant (see **Appendix 16**), to ensure the woman has understood the request. Women who do not demonstrate comprehension (e.g. require an interpreter for insufficient English or have intellectual disability) will be excluded from the trial.

This initial survey will take place in the hospital waiting room as not all hospitals have access to private rooms. Every effort will be made to ensure all conversations take place as discreetly as possible and are sensitive to the surrounds. Women who express interest in the study will be asked to provide signed, informed consent (see **Appendix 17**) before completing the screening questions. In our pilot of 118 women there were no concerns expressed by women in either being approached or completing the survey in the waiting room. This first consent process indicates that the woman is happy to participate in the screening survey, and to hear more about the RCT if eligible. If the screening survey shows that a woman is eligible for the RCT, the researcher will tell her this straight away (see script in **Appendix 16**) and ask her if she would like to hear more about the trial. Women who say yes will be told more about the study (see script in **Appendix 16**), given the baseline PIS&C and asked if they would like to read through the PIS&C then, or take it home. Women who provide informed baseline consent at that point will be asked for their contact details and asked if they would like to make a time for the first home visit then. Women who want to take the PIS&C home to read first will be asked if they are happy for the research team to phone them in a few days to follow-up. Women who say yes will be asked to complete a contact details slip (**Appendix 18**). Women who are not interested in hearing more, or who read the PIS&C and then decline participation, will be asked for a reason why (if they are happy to give a reason). Before a woman leaves the clinic, the researcher will give her a card (**Appendix 19**) with the study team's contact details, and encourage the woman to contact the team if they have any further questions about the study.

In the days following the antenatal screening survey, researchers will phone women who provided their contact details to answer any questions. Researchers will also ask whether the woman is part of the Victorian CtK program. Women who are part of the program will be informed that they are

ineligible for the right@home study, and will cease participation. Researchers will organise a suitable time for the first home visit with women who provide informed consent for the RCT (baseline PIS&C) at the antenatal clinic. Women who provided contact details but not informed consent will be asked if they are happy to take part and, for those who agree, the researchers will organise a time for the first home visit. For women who decline participation, researchers will record reasons why, if the woman is happy to specify.

*Enrolment:* At the enrolment home visit with the researcher, a signed consent form will be obtained for each participant before any further survey administration. Women younger than 18 years are not excluded from the study because they are part of the vulnerable population that this trial targets. These women will be making their own decisions about participation in health services for themselves and their child. Some pregnant young people are estranged from family and it would be inappropriate to require parental consent in these circumstances. In line with Section 4.2.9 of the National Statement, we will assess their understanding of the information by verbally going through the information sheet (this will be standard practice in this research as levels of English-language literacy will not be assumed), and then asking the young person (and indeed all participants) to reiterate to the researcher what they understand the research to involve and whether they needed further clarification. We believe this is best practice for this population and enables appropriate discussion of the consent process. In this way we would take steps to ensure participants understand the relevant information. . Furthermore, with regards to the rest of section 4.2.9, this research is low risk, is very likely to benefit the young person, and may be contrary to the best interests of the young person to seek consent from parents. Where the young woman would like to do so, we will also explain the research to, and gain consent from their parents.

The consent form will describe the purpose of the study, the procedures to be followed, and the risks and benefits of participation. The trained researcher will conduct the informed consent discussion and will check that the participant and their legally acceptable representative comprehend the information provided and answer any questions about the study. Consent will be voluntary and free from coercion. At all times it will be made clear that non-participation in the study will not affect the usual routine clinical management offered by any health providers, e.g. the care they receive from the hospital or as part of the maternal and child health service. The researcher who conducted the consent discussion will also sign the informed consent form. A copy of the consent form will be given to the participant or their legally acceptable representative and the fact that the participant has been consented to the study will be documented in the participant's record on the study's electronic database.

Following the baseline assessment and once all the inclusion and exclusion criteria have been addressed and the eligibility of the participant confirmed, allocation to the intervention or usual care arms will be conducted online by the research assistant using a web-based randomisation application set up by an independent statistician. We aim to recruit 20 participants (10 per arm) per week until the total number of participants is obtained. The research assistant will then inform the participant of their randomisation status.

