## 1.2 Study Management and Governance

The governance structure is presented in Figure 1. This trial will be conducted by three partners: ARACY, CHETRE and CCCH (the Partnership). The trial itself consists of 2 main streams of work: the programme (intervention) element and the research (evaluation) element. Although the Partnership is responsible for the trial overall, the programme element will be coordinated and lead by a team comprising the Project manager, Registered Nurse, Postdoctoral Researchers and Research Assistants based at ARACY (ACT) and CHETRE (NSW). The research element of the trial will be coordinated and lead by a team based at the CCCH comprising the Principal Investigator, Project Manager, Paediatrician, Statistician, Health Economist and Research Assistants. ARACY will have overall project management responsibility to ensure that the two streams of work remain coordinated when necessary.

Qualified maternal and child health nurses will deliver the intervention. Trained research assistants will conduct the informed consent discussions and clinical assessments with participating women and children. The project coordinator (ARACY) and CHETRE will be responsible for hiring and training nurses. The research manager (CCCH) will be responsible for organising recruitment, participant assessment and data maintenance and storage. The project manager (ARACY) and research manager (CCCH) will be responsible for creating and maintaining study documentation.

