## **4. STUDY DESIGN**

### **4.1 Type of Study**

This is a longitudinal, randomised controlled, multi-site evaluation of a sustained nurse home visiting program compared with usual care. The program will be offered to families from the antenatal period to the final follow-up assessment at child age 2 years. Researchers responsible for collecting the data, but not families or nurses, will be blinded to participating families' randomisation status.

A critical feature of the current trial is that it is designed based on strict program logic (see Figure 2 below), which is lacking in many of the previous home visiting randomised trials. A recent review by Segal et al (2012) of home visiting programs to reduce child maltreatment showed that programs based on strict program logic were much more likely to be effective than those that were not. As such, we are designing the trial to ensure any effects can be clearly traced back to the intervention offered. Specifically, the right@home intervention is based on the MECSH SNHV program, but is being enhanced to include evidence-based strategies on three focus modules which specifically target the three primary outcomes measured at age 2 years: parent care and responsivity, and a supportive home learning environment.

Figure 2: Program logic for the right@home trial

[figure not shown]

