### **6.3 Randomisation Procedures**

Patients will be randomly assigned to receive the treatment (home visiting intervention) or usual care arms. Families will be equally divided between the two arms, based on our sample size estimation (see Section 10.1). A statistician not directly involved in the analysis of the study results

will prepare the randomisation schedule using block randomisation to maintain balance between treatment arms. Randomisation will be stratified both by parity (1st time parent vs. those with children already) and site. The schedule will be administered using a web-based randomisation schedule to enable randomisation to be conducted remotely at each location. Sealed envelopes containing randomised treatment allocation will be provided to each study location in case of the event that the web based system cannot be accessed during the randomisation of a participant.

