#### **6.4 Blinding Arrangements**

The project manager, participants and nurses will be aware of the allocation to treatment arm to enable organisation for the mothers to receive the active or control intervention. Research staff responsible for conducting outcome assessments will be blinded to treatment allocation. Families will be asked not to disclose their randomisation status at assessments; however, those that do will be recorded in the study database and this 'unbinding' will be examined as a potential confounding variable in the outcome analyses.

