#### **Serious Adverse Event (SAE)**

An SAE is defined as any AE that:

- results in death; or
- is immediately life threatening; or
- requires inpatient hospitalisation; or
- requires prolongation of existing hospitalisation; or
- results in persistent or significant disability/incapacity; or
- is a congenital anomaly/birth defect.

Important medical events will be considered an SAE when, based upon appropriate medical judgement, they may jeopardize the patient and may require medical or surgical intervention to prevent one of the outcomes listed in this definition.

We recognise that participation in the right@home study may be a cause of potential stress or harm to participants, if it asks questions that are distressing, or if participation leads to disagreements or fights between the participant and her partner and/or family. Potential stress will be minimised in the following ways:

1. The participant will be fully aware of the reason for the questions asked in the assessments
2. The participant will be advised that they can decline to continue in the trial at any time
3. Participants will be offered appropriate referral for any concerns raised

At recruitment screening, any women who becomes distressed will be encouraged to discuss their concerns with the health provider they are about to see. During the study if a research assistant is

concerned about a parent they will discuss this with the PI. With the parent's permission a referral mechanism will be in place to the parent's local doctor or maternal and child health nurse. This process has been implemented successfully with a number of other studies that specifically ask about self harm behaviour. If the parent is within the intervention arm the PI will contact the parent and ask permission to refer back to the intervention nurse.

At the 6 week, 6 month and 18 month follow-up phone assessments, women will be asked what things they like and dislike about being part of the study, and whether being part of the study has caused them any harm so far. These questions will be developed based on previous MCRI studies that have successfully used these processes (e.g. Weave Study, Healthy Mothers Study) and submitted for approval in a future ethics modification.

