#### **11.2 Data Storage**

All participants and nurses will be given unique numerical identifiers (an ID code) for use throughout the study. A single, online electronic database will record all participant and nurse details. It will be hosted by the MCRI server, because it is secure and meets ethical confidentiality requirements. Nurses, researchers and managerial staff will have different levels of access to the password-protected database. Nurses will only be able to access the details of the families in their caseload; researchers will be able to access the details of families but not their randomisation status; and managerial staff will be able to access all levels as required. All participant and nurse questionnaire data will be identified by ID code only and be stored in the secure electronic database. Digital video

material (i.e. collected by intervention nurses to conduct video feedback with families) will be attached as electronic files to the family's record in the database. Any written materials will be scanned and also saved with the family's record on the electronic database. Hardcopy (paper) nurse materials will be stored in a locked cabinet at CHETRE, and hardcopy family materials will be stored in a locked cabinet at CCCH. Only project staff directly involved in the analysis of the data will have access to these materials and the electronic database. The database linking the participants' identity to their ID code will be maintained electronically on a password protected file.

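### Research assistants randomise, announce the arm and carry out assessments, and no rule keeps them from assessing families they randomised, so assessor blinding is claimed but not secured

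*Protocol*

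**What the plan says.** On who allocates, Protocol 6.1 (Enrolment) says: "allocation to the intervention or usual care arms will be conducted online by the research assistant using a web-based randomisation application". It continues: "The research assistant will then inform the participant of their randomisation status". Section 7 allows this to happen in the home at the end of the enrolment visit, or by phone.

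On who assesses, section 1.2 says: "Trained research assistants will conduct the informed consent discussions and clinical assessments with participating women and children". Section 7 assigns follow-up to the research team without naming separate staff.

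On who is blinded:
- 4.1: "Researchers responsible for collecting the data, but not families or nurses, will be blinded to participating families' randomisation status".
- 6.4: "Research staff responsible for conducting outcome assessments will be blinded to treatment allocation". It lists the project manager, participants and nurses as aware of the arm. Families are asked not to disclose. Disclosures are recorded and examined in the outcome analyses.
- 6.5.2: research staff receive the allocations once all 24-month primary assessments are complete.
- 11.2: "researchers will be able to access the details of families but not their randomisation status".

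**The concern.** One staff role generates the allocation, announces it and carries out assessments, while four sections say that this kind of staff does not know the arm.

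Mothers and nurses cannot be blinded in this trial, so protection of observer-rated measures against expectation bias rests largely on the assessor not knowing the arm. Table 2 makes the observational HOME responsivity subscale the only measure of the second primary outcome. The home safety audit, also observational, is part of the first. The third uses HOME subscales that are partly observational. If an assessor scores these knowing that a family had two years of nurse visits, a difference between arms could come partly from the scoring.

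**Working it through.** No arithmetic applies. The sample size in 10.1 does not depend on this point, and the protocol gives no figure for assessor bias. The check is a comparison of the text.

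1. **Does the allocating role know the arm?** Yes. In 6.1 the research assistant performs the allocation and tells the mother the result.

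2. **Does the same role do outcome assessments?** Yes, as a role. Section 1.2 refers to assessments of women and children. Women enrol while pregnant, so assessing children can only mean postnatal follow-up.

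3. **Are the two tasks separated anywhere?** Sections 1.2, 6.1, 6.3, 6.4, 7, 8 and 11.2 contain no statement that follow-up assessors differ from enrolling staff, and none that a research assistant may not assess a family they randomised.

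4. **Comparison with each blinding statement:**

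| Section | What it states | Against 6.1 |
|---|---|---|
| 4.1 | Data collectors are blinded | The role that collects baseline data goes on to allocate |
| 6.4, list of those aware | Project manager, participants, nurses | The allocating research assistant is missing |
| 6.4, assessor rule | Outcome assessors are blinded | Can be met only if assessors never see families they randomised, which is not stated |
| 6.5.2 | Research staff learn the arm after the 24-month assessments | Research assistants learn it at enrolment |
| 11.2 | Researchers cannot access randomisation status | Research assistants produce it |

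One caution on 6.5.2: its wording could be read as covering only staff who do the analysis. On that reading it does not conflict. The other rows do not depend on it.

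5. **Do the safeguards in 6.4 cover this route?** No. Both act on disclosure by the family at an assessment. An assessor who made the allocation already knows the arm, so no disclosure need occur and none is recorded. The planned examination of unblinding would then count that family as assessed blind.

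**The case against.** The strongest reply is that the overlap is by role and not by person. Section 1.2 is a governance summary of staff types, and 6.4 sets a rule for whoever conducts the outcome assessments. Primary outcomes are measured at child age 2, more than two years after enrolment, and rostering could send a different research assistant. This stands. A reader might infer that assessor blinding fails, but the documents do not say that the same person randomises and later assesses a family. They support only that the separation is not stated and that the lists of who knows the arm are wrong.

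A reader might also see other leaks. None of these shows that blinding fails:
- **Nurse videos.** Section 11.2 attaches them to the family's record but also gives nurses, researchers and managers different access levels. It does not say that assessors can open them. Section 5.2 already shields the fidelity checklists from assessing researchers.
- **Phone questions.** Under 9.1, "women will be asked what things they like and dislike about being part of the study", but at 6 weeks, 6 months and 18 months. The observational ratings are made at the 12- and 24-month home visits.
- **Tracing through nurses (10.1).** The text does not say that assessors do it.
- **Backup envelopes (6.3).** They are sealed, for use only if the web system is down, and bear on allocation concealment rather than assessor blinding.

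Finally, several primary measures are reported by the parent: the sleep item, the mealtime diary, CHAOS, MCDI and part of HOME. Assessor blinding protects these much less. That also stands, and it limits the point mainly to the observed measures.

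**Conclusion.** The point holds as an internal contradiction with a missing safeguard. Section 6.1, read with 1.2, conflicts with 4.1, with 6.4's list of who is aware, with 11.2 and, on its plain reading, with 6.5.2. Those statements would still misdescribe who knows the arm even if follow-up went to other people. Blinding for HOME responsivity, the observed HOME items and the home safety audit is asserted, but no stated procedure delivers it.

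The conclusion rests on the protocol text alone. It assumes that no separation rule exists in a document not shown. An inflated false-positive rate should not be attached to it: that would need an assumed scoring shift and an assumed share of families assessed by someone who knew the arm, and the protocol supports neither.

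It should be settled before enrolment starts, because a research assistant who has announced an arm cannot be blinded to it again.

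**What to change.** Choose one of two arrangements and write it into 6.1:

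1. **Preferred.** Allocation and its disclosure are done by someone who takes no part in outcome assessment. The project manager, already unblinded under 6.4, could do this by phone, an option section 7 foresees. Section 1.2 places a project manager in both the programme team and the research team, so the text should say which one is meant.
2. **If research assistants keep the task.** State that no one assesses a family they randomised or whose arm they know, and roster the 12- and 24-month home visits on that basis.

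Then bring 4.1, 6.4, 6.5.2 and 11.2 into line, listing whoever allocates as aware of the arm. Add to 11.2 that the nurse videos are closed to assessors, as 5.2 already provides for the fidelity checklists.

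Cost: wording, database access rights and task assignment. Under the first option the mother may learn her arm slightly later, and the project manager takes on allocations at the planned 20 per week. Under the second, rostering is a little more constrained. The sample size, outcomes and analysis are unchanged.
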